### Statistical analysis

The primary analysis will include all women who consented to study participation and gave information on her intention to participate in a potential mammography screening (full analysis set). It consists of a likelihood ratio chi-square test of the intention to screening participation with a two-sided alpha of 5%. As a sensitivity analysis, best and worst case analyses will be performed in all consenting women (intention-to-treat population) with different imputations for missing values. In a second step, a logistic regression model including potential confounders and effect modifiers (for example, knowledge) will be fitted to the data for further explanation of the primary result. Secondary endpoints (knowledge, self-assessed knowledge, importance of knowledge, confidence in decision) will be compared using chi-square tests or Mann–Whitney *U* tests, whichever appropriate.

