## Methods

This is a controlled two-armed single-blind questionnaire study. Women will be randomized into two groups: group A will receive the 'new brochure’ (Additional file 1) with facts and figures corresponding to current evidence on outcome. Group B will receive the 'old brochure’ (Additional file 2) with little, merely promoting, information.

We are addressing women aged 48 to 49 yrs, that is, one or two years before eligibility for mammography screening. For ethical reasons we did not choose the eligible age, so as not to influence the immediate decision of the women regarding participation in screening. Also, women aged 50+ are more likely to have received and studied the 'new brochure’ already, so the study’s control arm receiving the 'old brochure’ would probably have been contaminated. The women are recruited via their GPs, whom we contact with a request to participate in the study. Twenty-five of 106 doctors contacted in the North Rhine-Westphalia area of Germany agreed to participate in the study and to send us a list of all women of eligible age who had presented to their practice in the past two years. In Germany, women of this age group (48 to 49 years) contact their GP about four times a year on average [18].

To pseudonymize the women, all names are deleted from the list before it is sent to us, while the internal practice reference number remains for later identification. We then randomly select 24 women from each practice for inclusion in the study. Randomization is at patient level, that is, these 24 women are randomized per practice into two groups; A ('new brochure’) or B ('old brochure’). According to the random allocation, the women in groups A and B will receive the respective brochure, a letter, and a uniform questionnaire about knowledge and intention to take part in a screening. Closed envelopes which are marked only by the internal practice reference number are sent to the practices and from there directly to the women. With the attached letter they are asked to complete the questionnaire after reading the brochure and to send it back to us, without disclosing their identity, for pseudonymous analysis. The questionnaires contain a reference number that can only be decoded by the GPs.

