#### ***Questionnaire***

The questionnaire employed to elicit the women’s knowledge has been developed on the basis of already existing, partly validated questionnaires [12-15,17] and builds upon the criteria for relevant knowledge to make an informed decision [2] (Additional file 3). It contains five questions on *knowledge* (one point for every correct answer) [2,14]. Two questions measure *the women’s self-assessment of their knowledge* about mammography screening; two questions are about the perceived *relevance of knowledge* for the individual [12]. There is one yes/no question on the intention to participate (primary outcome), combined with a confidence rating for this decision (six-point scale from 'very unsure’ to 'absolutely sure’). Furthermore, there is one question each about personal experience with breast cancer, educational level, age, marital status and native language, two questions concerning the assessment of the brochure, and an open question for the participant to indicate information needs not sufficiently dealt with in the respective brochure. For secondary analyses we constructed items on the following topics: preferred media for support in screening decision, risk perception, attitudes towards mammography screening.

The questionnaire was pre-tested in 15 women with regard to comprehensibility, resulting in slight revisions of item wording and scaling.

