### Sample size

At present, the participation rate for mammography screening in North Rhine-Westphalia, Germany is 53.7% [20]. We assume that participation in this interview study is more likely than participation in real screening, and therefore expect a 60% willingness to take part on mammography screening in the interviews. We judge a group difference of at least 15 absolute percentage points (that is, from 60% to 75% or from 60% to 45%) to be relevant. To detect such differences in the primary analysis with a power of 80%, 173 study participants per group = 346 participants have to be included. We expect a response rate of approximately 50%, so at least 692 women need to be contacted.

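### Women are randomised within practice, but no stated analysis accounts for practice; the pooled primary test is valid, and may be mildly conservative and lose some power if practices differ (minor)

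*Protocol article*

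**What the plan says.** Design (protocol article, Methods). Practices supply lists of eligible women: "Twenty-five of 106 doctors contacted in the North Rhine-Westphalia area of Germany agreed to participate in the study". Then "We then randomly select 24 women from each practice for inclusion in the study", and "Randomization is at patient level, that is, these 24 women are randomized per practice into two groups". The unit of randomisation is the woman, and the allocation is made separately in each practice. The text does not say whether each practice is split 12:12 or each woman is allocated independently.

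Outcome (Questionnaire). "There is one yes/no question on the intention to participate (primary outcome").

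Analysis (Statistical analysis). The primary test is fixed: "It consists of a likelihood ratio chi-square test of the intention to screening participation with a two-sided alpha of 5" per cent. The listed sensitivity analyses are best-case and worst-case imputations of missing answers. As a second step, "a logistic regression model including potential confounders and effect modifiers (for example, knowledge) will be fitted to the data for further explanation". Practice appears in none of these.

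Sample size. The trial is sized as a plain comparison of two proportions: 60% against 45% or 75%, 80% power, 173 per group, 50% response, at least 692 women contacted.

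**The concern.** An analysis should normally reflect the factors that randomisation was restricted by. If willingness to be screened varies between practices, through the doctor's attitude or the social mix of the patients, a design that balances the groups within each practice removes much of that variation from the comparison between brochures. The pooled chi-square test still counts it as noise. Its reference variance is then too large, its true type I error lies below 5%, and some power is given up. A missing covariate list could be left to a separate analysis plan. Here, however, the article names the primary test itself, and that test does not reflect the design described a few paragraphs earlier.

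What is at stake is efficiency and agreement between design and analysis. The risk of a false positive finding is not raised.

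**Working it through.** **1. The plan's own figure.** With p₁ = 0.60, p₂ = 0.45 and mean 0.525, the pooled-variance formula gives

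n = [1.960·√(2·0.525·0.475) + 0.842·√(0.60·0.40 + 0.45·0.55)]² / 0.15² = [1.384 + 0.588]² / 0.0225 ≈ 172.8, so 173 per group.

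This reproduces the stated number, and 346 / 0.5 = 692. The sample size therefore assumes an unstratified test, as does the analysis section.

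**2. When the pooled test is conservative.** Inputs from the article: 25 practices, 24 women each, 50% response, hence 25 × 24 × 0.5 = 300 responders, or about 150 per group. Assumed: the ICC ρ of intention within practice, taken over 0 to 0.20, and the split within practice. With no brochure effect, the variance of the difference in proportions is

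p(1−p)·[(1−ρ)(1/N_A + 1/N_B) + ρ·Σ(n_Ak/N_A − n_Bk/N_B)²],

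where n_Ak and n_Bk are the responders of each group in practice k. The pooled test uses p(1−p)(1/N_A + 1/N_B), where 1/N_A + 1/N_B = 2/150 = 0.0133.

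- *12:12 split.* n_Ak and n_Bk each have variance 12·0.5·0.5 = 3, so their difference has variance 6. The sum is about 25·6/150² = 0.0067, half of 0.0133. The ratio of true to assumed variance is R = (1−ρ) + 0.5ρ = 1 − 0.5ρ.
- *Independent allocation of each woman.* Each woman adds +1 or −1 to the difference with probability 0.25 each (variance 0.5), so 24 women give 12. The sum is about 25·12/150² = 0.0133 and R = 1. The test is nominal at every ICC.
- *Full balance among responders.* The sum is 0 and R = 1 − ρ. Non-response thus pulls the test back towards its nominal level.

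Type I error is 2[1 − Φ(1.96/√R)]. For the 12:12 split this gives:

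- ρ = 0.05: R = 0.975, 0.047
- ρ = 0.10: R = 0.95, 0.044
- ρ = 0.20: R = 0.90, 0.039

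**3. Simulation of the documented design.** Settings: 25 × 24, 12:12 assumed, 50% response, beta-distributed practice rates with mean 60%, 60% against 45%. The pooled likelihood ratio test is set against a practice-stratified Cochran-Mantel-Haenszel (CMH) test. The type I column gives the range over repeated runs; Monte Carlo error is about 0.001 for type I error and 0.002 for power.

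| ICC (assumed) | Pooled type I error | Power, pooled | Power, CMH |
|---|---|---|---|
| 0 | 0.051 | 74.3% | 72.3% |
| 0.02 | 0.050 | 74.3% | 72.9% |
| 0.05 | 0.045–0.050 | 74.6% | 74.4% |
| 0.10 | 0.043–0.046 | 74.7% | 76.5% |
| 0.20 | 0.039–0.040 | 75.2% | 81.2% |

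With independent allocation inside practices (simulated with 29 practices), the pooled type I error stays between 0.049 and 0.051 throughout, as step 2 predicts. CMH then costs up to 4 points of power at low ICC, breaks even nearer ICC 0.10, and still gains at 0.20 (80.2% against 74.6%).

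**4. At the planned size.** With 29 practices (29 × 24 = 696 mailed, about 173 responders per group) and a 12:12 split, power for pooled against CMH is 79.9% and 78.0% at ICC 0, 80.3% and 80.2% at 0.05, 80.8% and 82.4% at 0.10, and 81.6% and 86.7% at 0.20. The break-even point is again near 0.05.

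**The case against.** The strongest reply is that the plan is coherent as it stands. The test is valid, it matches the sample-size calculation exactly, and any error is in the safe direction. The conservatism needs two conditions that the article does not state: material variation between practices, and balance within practice. If either is absent, the pooled test holds its 5% level. With about six responders per group per practice, stratifying can also lose power when practices hardly differ. All of this stands, and it is why the point is minor. It does not remove the mismatch: the randomisation is described as made per practice, and no analysis, primary or sensitivity, uses practice.

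Four stronger readings are tempting, and the article does not support them.

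- A reader might infer that the error rate certainly falls below nominal. That depends on an ICC and a split that are not given.
- A reader might infer that clustering by practice calls for a design effect or a larger sample. Both brochures are randomised within each practice, so practice variation does not inflate the variance of the comparison, and 173 per group is unaffected.
- A reader might infer that the planned confidence interval is too wide. The section states no interval.
- A reader might use the gap between 25 × 24 = 600 and the 692 to be contacted as evidence. That gap explains why the power figures above are near 74%, but it is a separate matter and does not show that the test is the wrong one.

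**Conclusion.** The point holds as a minor one, on efficiency and on consistency of analysis with design. If practices differ and the groups are balanced within practice, the pooled test runs at about 0.045 to 0.047 at ICC 0.05 to 0.10 and about 0.040 at ICC 0.20. It then gives up about 2 points of power at ICC 0.10 and about 6 at 0.20. At ICC 0.05 or below there is nothing to gain from stratifying. These sizes rest on an assumed ICC, an assumed 12:12 split, and a 50% response that is unrelated to practice or brochure. The direction is safe in every scenario examined: type I error was never materially above 5%.

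**What to change.** Before unblinded analysis, prespecify an analysis of intention that accounts for practice. A logistic model with a random intercept for practice is preferable, because it moves towards the ordinary model when practices hardly differ. The alternative is a practice-stratified Cochran-Mantel-Haenszel test with a common risk difference and 95% confidence interval. Either can be the primary analysis or a named sensitivity analysis beside the likelihood ratio test; the choice should be fixed in writing without sight of results by group. Include practice in the second-step logistic model as well.

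The cost is a line or two of wording. Confirm that the analysis file retains the practice: the team randomised practice by practice, but the article says that only the doctors can decode the questionnaire's reference number, and it does not say that the number identifies the practice to the analysts.

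If CMH is made primary, it costs about 1 to 2 points of power at ICC 0 to 0.02 with a 12:12 split, and up to 4 with independent allocation. Practices with replies from one group only contribute nothing to it. With twelve women mailed per group and a uniform 50% response that would be rare (2 × 25 × 0.5¹² ≈ 0.01 practices expected), but it becomes more likely if response is very low in some practices.

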### Research questions

We wanted to know whether, and to what extent, the content of the information brochure distributed nationwide in Germany influences women’s intention to participate in mammography screening, and whether EBPI-relevant, transparent information regarding the potential benefits and harms of early detection screening influences this intention. In detail, our research questions are:

1. What influence does an information brochure including relevant facts and figures on the harms and benefits of mammography screening ('new brochure’) have on women’s intention to take part in screening, compared to a brochure that mainly promotes the screening while omitting relevant information ('old brochure’)?

2. Do different information brochures lead to different knowledge about the potential benefits and harms of mammography screening?

3. Are there any other factors (beside the contents of brochures) influencing the decision to take part (for example, personal experience with breast cancer, marital status)?

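### The unadjusted primary test is valid and meets its stated power, but it leaves unused the practice stratum and the fixed characteristics already collected

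*Protocol article*

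**What the plan says.** **Primary test.** Statistical analysis defines it without covariates: "It consists of a likelihood ratio chi-square test of the intention to screening participation with a two-sided alpha of 5" per cent. The analysis set is the consenting women who answered the intention item.

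**Later model.** The same section continues: "In a second step, a logistic regression model including potential confounders and effect modifiers (for example, knowledge) will be fitted". Its stated purpose is to explain the primary result further. Knowledge also appears there as a secondary endpoint.

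**Randomisation.** Methods says that 24 women per practice are selected and randomised to the two brochures within their practice, so practice is the randomisation stratum. Brochure and questionnaire go out in the same mailing.

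**What is recorded.** Under Questionnaire, "there is one question each about personal experience with breast cancer, educational level, age, marital status and native language".

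**What is said about influence.** Research question 3 asks: "Are there any other factors (beside the contents of brochures) influencing the decision to take part". It gives breast cancer experience and marital status as examples.

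**Response.** Sample size: "We expect a response rate of approximately 50%, so at least 692 women need to be contacted".

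**The concern.** A binary endpoint tested without covariates gives up precision when baseline factors predict it. Here the candidate factors cost nothing, because every responder is asked for them. A mailed brochure cannot change schooling, marital status, native language or past experience with breast cancer. Randomisation within practice is a second reason to adjust, since the usual principle is to analyse as randomised.

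Response adds a further reason. A woman replies, or does not, after receiving her allocated brochure, and about half are expected not to reply. Randomisation balances the women who are mailed; it does not guarantee balance among those who answer. If the two brochures draw replies from different kinds of women, the unadjusted difference contains part of that difference.

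The second-step regression, as described, does not supply the adjusted estimate. Knowledge lies on the path from brochure to intention (research question 2 asks whether the brochures change it). A model conditioning on knowledge therefore does not estimate the total brochure effect, which is what the hypothesis concerns.

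**Working it through.** **1. Reproduce the plan's figure.** Inputs from Sample size: "expect a 60% willingness to take part on mammography screening in the interviews", a relevant difference of 15 points in either direction, and "with a power of 80%, 173 study participants per group = 346 participants have to be included". The two-sided 5% level is from Statistical analysis. Pooled-variance formula, no continuity correction:

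n = [1.960·√(2p̄(1−p̄)) + 0.842·√(p₁(1−p₁)+p₂(1−p₂))]² / (p₁−p₂)²

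- 60% vs 45%: p̄ = 0.525, so n = [(1.384 + 0.588)/0.15]² = 172.8, rounded up to **173**, an exact match.
- 60% vs 75%: n = 152, so 173 gives 84.9% power.
- Contacts: 346/0.5 = 692, as stated.

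Simulating the likelihood ratio test itself at 173 per group (400,000 runs) gives 79.2% power for 60% vs 45% and a type I error of 5.2%. The planned test does what the plan says.

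**2. Power with adjustment, by formula.** Covariate strength is an assumption: R², the share of variance in intention explained, is varied over 5-15%. Effective n per group is 173/(1−R²), for 60% vs 45%.

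| R² | Effective n | Power |
|---|---|---|
| 0 | 173 | 80.0% |
| 5% | 182 | 82.0% |
| 10% | 192 | 84.0% |
| 15% | 204 | 86.0% |

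**3. Power with adjustment, by simulation.** Likelihood ratio chi-square versus the likelihood ratio test from a logistic model with five baseline covariates, 173 per group, marginal rates held at 60% and 45%, 3,000 runs (simulation error about 0.7 points).

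| R² | Unadjusted | Adjusted |
|---|---|---|
| 0 | 79.9% | 80.5% |
| 0.04 | 78.7% | 81.3% |
| 0.10 | 77.9% | 82.4% |
| 0.17 | 79.1% | 86.6% |

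Type I error was about 4-6% for both tests (1,500 runs, simulation error about 0.6 points). The simulation agrees with the formula: a few points of gain if the factors predict intention, no real change if they do not. Practice was not simulated, so any gain from including it is not in these figures.

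**4. Responder imbalance (assumed values).** Bias in the difference = effect of the factor on intention × gap in its prevalence between the responding groups.

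- 15-25 points × 5-10 points of gap: 0.15×0.05 = 0.75 points, up to 0.25×0.10 = 2.5 points.
- 20-30 points × 10 points of gap: 2-3 points.

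The standard error of the difference at 60% is √(2×0.6×0.4/173) = 5.3 points. A systematic bias of 2-3 points would raise the type I error from 5% to 6.7-8.8%.

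Chance alone gives a prevalence gap with standard deviation √(2×0.3×0.7/173) = 4.9 points for a factor present in 30%. The unadjusted test already allows for chance gaps in its error rate. Only a systematic gap from brochure-dependent response biases it.

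**The case against.** The strongest reply is that nothing here is wrong. An unadjusted test is a legitimate primary analysis in a trial randomised by patient, it matches the sample size calculation, and it delivers the stated power. **This stands.** A reader might infer that the trial is underpowered or that the test is faulty; step 1 shows otherwise.

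Second, the plan does not ignore covariates: a regression with potential confounders follows, the mention of knowledge is only an example, and a covariate list normally belongs in the analysis plan. **This stands in part.** The missing list is not the point. The point is that the article fixes the primary test as unadjusted and gives the regression an explanatory role, with a post-brochure variable as its one named covariate.

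Third, one might infer from research question 3 that the plan itself regards these factors as prognostic. **It does not.** The question is open, and its examples do not include education or native language. All gains above are therefore conditional.

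Fourth, one might infer that adjustment cures bias from selective response. **It does not.** If reply depends on the brochure together with an unrecorded prior attitude to screening, adjusting for schooling or marital status will not restore comparability. The planned best and worst case analyses cover consenting women only, so they do not reach the non-responders either. Nothing in the document indicates that response will differ between arms.

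Last, adjustment has costs. A logistic test is conditional while a standardised risk difference is marginal, so the two can disagree near the 5% threshold. Native language may be sparse, because women with insufficient German are excluded. Both stand and are handled under the fix.

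**Conclusion.** The point holds as a missed gain, not as an error. The primary test is valid and has 80% power at 173 per group for 60% vs 45%. Adjusting for practice and the recorded fixed characteristics would raise that to about 82-86% if these characteristics explain 5-15% of the variance in intention, and would leave it essentially unchanged if they explain none. That range is assumed; the document gives no covariate strength.

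Adjustment would also remove responder imbalance on the recorded factors, worth perhaps 1-3 points against a 15-point target. That too rests on assumed effects and prevalence gaps. The second-step regression does not provide the same estimate as long as knowledge is in it. Label: cheap improvement.

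**What to change.** Before the data are analysed, amend Statistical analysis as follows:

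- Make the primary test the likelihood ratio test for brochure, two-sided 5%, in a logistic model with brochure, practice (for example as a random intercept), educational level, personal experience with breast cancer, marital status and native language.
- Exclude knowledge, attitudes, risk perception and confidence in the decision, all of which the brochure may change. They can stay in the explanatory second-step model.
- State in advance how sparse categories are merged, and code a missing covariate answer as its own category so that no woman is lost.
- Report the standardised risk difference with its 95% confidence interval, so that the result can be read against the 15-point target. State in advance that the test decides if test and interval disagree.
- Keep the unadjusted chi-square test as a supportive analysis.

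The cost is wording: the variables are already on the questionnaire and the sample size need not change. The downsides are that the primary result is no longer a plain two-by-two table, that a few degrees of freedom are used, and that the conditional test and marginal interval may occasionally differ near the threshold.

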### Consent and ethical approval

All participants will be asked for informed consent to participate.

The study was approved by the ethics committee of the University Hospital, Heinrich-Heine-University of Duesseldorf (22.02.2012, ref. number 3797) (Additional file 4).

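### The set called intention-to-treat contains only consenting women, so the best/worst-case analysis cannot address the roughly 50% of randomised women expected not to respond

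*Protocol article*

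**What the plan says.** The order of events is given in the Methods section of the protocol article. Practices send pseudonymised lists, 24 women per practice are drawn at random, and "these 24 women are randomized per practice into two groups". After allocation, "the women in groups A and B will receive the respective brochure, a letter, and a uniform questionnaire about knowledge and intention". The reply comes last: "they are asked to complete the questionnaire after reading the brochure and to send it back to us".

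On consent, the Consent and ethical approval section says only that "All participants will be asked for informed consent to participate". It gives no time point, and no contact with the women before the mailing is described anywhere.

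The Sample size section sets 173 participants per group (346 in total) and then states "We expect a response rate of approximately 50" per cent, which leads to 692 women to be contacted.

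The Statistical analysis section defines two sets. The primary (full analysis) set is women who consented and answered the intention question. The second is used for sensitivity analysis: "best and worst case analyses will be performed in all consenting women (intention-to-treat population) with different imputations for missing values". The Limitations section deals only with the formal design of the brochures and does not mention non-response.

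**The concern.** An intention-to-treat set contains those who were randomised. Here the label is attached to women who consented, and consent and return appear to come after allocation. The two sets in the plan therefore differ only by consenters who did not answer the intention item. Women who return nothing are in neither.

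This matters because one brochure mainly promotes screening and the other sets out harms such as overdiagnosis and false positives (Table 1). The brochure could influence who replies, and replying could be related to intention, which is the primary outcome. In that case the responders in the two arms are no longer comparable, and a difference in intention could be created or masked. The only missing-data check stated in the article would not touch this, yet its label suggests that it does. The set is defined in the text, so this is not a detail left to a fuller document.

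**Working it through.** **1. The plan's own figures.** Inputs from the Sample size and Statistical analysis sections: 60% vs 45%, two-sided alpha 5%, power 80%, 1:1.

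n = [1.96·√(2·0.525·0.475) + 0.8416·√(0.6·0.4 + 0.45·0.55)]² / 0.15² = (1.3842 + 0.5876)² / 0.0225 = 172.8, so 173 per group. The stated figure is reproduced. The other direction (60% vs 75%) needs 152, so 173 is the larger. Contacts: 346 / 0.5 = 692, also reproduced. The sample-size arithmetic is not in question.

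**2. Who is outside the so-called intention-to-treat set.** 692 − 346 = 346 women, or 50% of those randomised.

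**3. What the planned best/worst case can move.** Let m be the share of consenters with a blank intention item, equal in both arms. The range is (1 − m)(pA − pB) ± m. The article gives no m; 2% and 5% are assumptions.

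| Responders A vs B | m = 2% | m = 5% | All randomised, 50% non-response |
|---|---|---|---|
| 60% vs 60% | −2 to +2 points | −5 to +5 | −50 to +50 |
| 45% vs 60% | −16.7 to −12.7 | −19.3 to −9.3 | −57.5 to +42.5 |

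The last column uses the same formula with m = 0.5, for example 0.5·(−0.15) ± 0.5. The planned check covers only the narrow columns.

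**4. What selective response could do (illustration).** Assume true intention of 60% in both arms, 50% overall response in both arms, and 173 responders per arm. With response probability r1 among intenders and r0 among non-intenders, the observed rate is 0.6·r1 / (0.6·r1 + 0.4·r0). All response probabilities are assumptions.

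- Arm A 45% / 57.5%, arm B unrelated to intention: 0.27 / 0.50 = 54% vs 60%. Under the null, SE = √(0.57·0.43·2/173) = 0.0532; under the alternative, √((0.2484 + 0.24)/173) = 0.0531. Rejection ≈ Φ((0.06 − 1.96·0.0532)/0.0531) = Φ(−0.83) ≈ 0.20.
- Arm A 40% / 65%, arm B unrelated: 0.24 / 0.50 = 48% vs 60%. SEs are 0.0536 and 0.0532. Rejection ≈ Φ((0.12 − 0.1050)/0.0532) = Φ(0.28) ≈ 0.61.
- Arm A unrelated, arm B 55% / 42.5%: 60% vs 66%, rejection about 21%.
- Arm A 45% / 57.5%, arm B 55% / 42.5%: 54% vs 66%, rejection about 63%.

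The overall return rate is 50% in both arms throughout, so comparing return rates would show nothing.

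**5. What a graded analysis would show.** With 50% response, the all-randomised rate in an arm is 0.5·p + 0.5·q. Here p is the rate in responders and q = OR·p / (1 − p + OR·p) the rate in non-responders. Suppose responders show 45% vs 60%.

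- OR 0.5 in A and 2 in B: q = 29.0% and 75.0%; overall 37.0% vs 67.5%, a difference of −30.5 points.
- OR 2 in A and 0.5 in B: q = 62.1% and 42.9%; overall 53.5% vs 51.4%, a difference of +2.1 points.
- The point estimate is zero when qA − qB = +15 points. If non-responders in B match responders (60%), this needs qA = 75%, an OR of (0.75/0.25)/(0.45/0.55) = 3.67.

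The range 0.5 to 2 is also an assumption; nothing in the article supports a particular range.

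**The case against.** Several counter-arguments carry weight.

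- *The set is openly described.* The same sentence says who is in it, so a careful reader knows. True, but the label still claims something the set does not have, and the imputation is still confined to it.
- *No analysis recovers the missing outcome.* Intention exists only on a returned questionnaire, and full best/worst bounds of ±50 points decide nothing. This stands. It is why the remedy is a graded analysis with a tipping point, and why the result must be described as conditional on responding.
- *The graded analysis can also overturn the target effect.* With odds ratios of 2 and 0.5 the 15-point difference disappears. This stands too. The analysis would show how fragile the result is and would not protect it, but readers can then weigh how plausible the required departure is.
- *The magnitudes are built on assumptions.* They are. The article gives no response rate by intention, and the scenarios use exactly offsetting rates. Those same scenarios mean that a test of return rates by arm could not serve as the safeguard.

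A reader might infer more than the text supports: that the comparison is biased, that differential response is the main threat to the trial, or that every non-responder declined after reading the brochure. None of this is established. Brochure-dependent response is only a possibility, nothing in the article ranks it against other threats, and some women may never open the envelope. The moment of consent is itself inferred from the mailing procedure, since the consent section does not state it.

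**Conclusion.** The concern holds as a wrongly defined analysis set and a sensitivity analysis of too narrow scope. About half of the randomised women (346 of 692 by the article's figures) are outside the set called intention-to-treat. The best/worst-case imputation reaches only unanswered intention items among consenters, worth about ±2 to ±5 points around no difference if 2% to 5% are blank (assumed).

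Under assumed selective response with equal return rates, the 5% test could reject a true null about 20% of the time (54% vs 60%) or 61% (48% vs 60%), and the planned check would not reveal it. These figures show what is possible and do not predict what will happen.

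The conclusion rests on the described sequence of randomisation, mailing and reply, and on the absence of any described consent step before mailing. The primary test and the sample-size calculation are not faulted by this point. It should be fixed, but it does not reach the level of a fault that must be cured before the trial can be interpreted at all.

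**What to change.** 1. Rename the current set *consenting responders*, and define the intention-to-treat set as all women randomised.
2. Keep the best/worst-case imputation, described as a check on item non-response among consenting responders.
3. Add a sensitivity analysis over all randomised women that varies intention among non-responders separately by arm and reports the tipping point at which the conclusion changes. State the range examined and label it as an assumption.
4. Report return rates by arm as description, noting that equal rates do not exclude bias.
5. State that the primary result is conditional on responding.

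The cost is wording and a few lines of analysis. No new data are needed, because allocation is made per practice and envelopes and questionnaires carry a reference number. Practices do the onward mailing and no feedback on what was actually sent is described, so the denominator should be women randomised, not women confirmed as mailed. The trial is still recruiting according to its status statement, so the change can be made before the arms are compared. The downside is a less reassuring sensitivity result.
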